### Outcomes {12}

The primary outcome is change in Insomnia Severity Index (ISI) score, measured as change from baseline to day 14.

Secondary outcomes include change in alcohol craving score from baseline to days 7 and 14, percent of total days abstinent during the 14-day practice quit attempt, mean number of drinks per drinking day as measured by the Timeline Follow Back, and change in PTSD symptoms as measured by change from baseline to days 7 and 14 in the CAPS-5 and PCL-5 score(s).

Exploratory outcomes include actigraphy sleep metrics for sleep latency onset (SLO), wake after sleep onset (WASO), and total sleep duration, as well as the change in PROMIS Sleep Disturbance *T*-score from baseline to day 14.

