### Sample size {14}

Sample size for this study was determined based on the prior published studies of suvorexant effect on ISI which suggest that the standard deviation (SD) is between 6 and 8 points for the change from baseline. Based on a two-sided *t*-test of treatment effect with 80% power and alpha set at 0.05, the study would be able to detect a medium effect size (about 0.66, e.g., mean difference of 5.5 with SD of 7) with a total of 76 participants. This total number of participants includes those that complete screening, placebo lead-in, and at least day 0 study activities through randomization (and assuming no more than 7% attrition/loss to follow-up).

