## Statistical methods

### Statistical methods for primary and secondary outcomes {20a}

The study will test the single hypothesis that change in ISI score between baseline and day 14 differs between suvorexant and placebo at 14 days using a 0.05 significance level. We will also test treatment differences for five secondary measures: change in AUQ score, change in PCL-5 and CAPS-5 score, comparison of number of mean drinks per drinking day, and count of days with no alcohol consumption. Secondary analyses will be adjusted for multiple comparisons using the Benjamini-Hochberg false discovery rate correction to maintain the nominal alpha level of 0.05. All other statistical comparisons will be descriptive. All analyses will be based on the intention-to-treat population, and no other analysis populations are planned. All analysis and methods will be fully detailed in the study’s Statistical Analysis Plan (SAP).

For the primary outcome, comparison of the change in ISI score from baseline to day 14 between treatment groups will be analyzed using a linear model for continuous outcomes that accounts for treatment, site, sex, and baseline ISI score (see proposed model). Adjusted estimates of the change in ISI score between treatment and within treatment and corresponding 95% confidence intervals will be produced.$$\mathrm{Y}_{\mathrm{i}} = \upbeta_{0} + \upbeta_{1}\mathrm{Treatment}_{\mathrm{i}} + \upbeta_{2}\mathrm{Site}_{\mathrm{i}} + \upbeta_{3}\mathrm{Sex}_{\mathrm{i}} + \upbeta_{4}\text{Baseline ISI} + \epsilon_{\mathrm{i}}$$where *Y*_*i*_ is the change in ISI score from baseline to day 14, *β*_0_ is the intercept, *β*_1_ through *β*_4_ are coefficients, and *ε*_*i*_ is the error term which is assumed normally distributed.

A similar model will also be run for the secondary outcome of mean number of drinks per drinking day, while a Poisson model will be explored for the number and percent of days abstinent during the 13-day quit attempt period, accounting for treatment, site, sex, and baseline ISI score.

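### Days abstinent is a count capped at 13 or 14 days; the Poisson model proposed for it gives wrong standard errors unless its variance is estimated

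*Protocol article*

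**What the plan says.** Outcomes {12} lists as a secondary outcome the "percent of total days abstinent during the 14-day practice quit attempt". Statistical methods {20a} names the tested secondary measures, ending with "comparison of number of mean drinks per drinking day, and count of days with no alcohol consumption". It then states: "Secondary analyses will be adjusted for multiple comparisons using the Benjamini-Hochberg false discovery rate correction to maintain the nominal alpha level of 0.05".

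The model sentence in the same section reads: "a Poisson model will be explored for the number and percent of days abstinent during the 13-day quit attempt period". The covariates are treatment, site, sex and baseline ISI. No offset, dispersion term or robust variance is mentioned, and details are deferred to an analysis plan that is not shown. Section {20c} says in general terms that secondary outcomes use a repeated-measures mixed model. A single total per person is not a repeated measure, so Poisson remains the only model named for this outcome.

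The two sections give different denominators: 14 days in {12}, 13 days in {20a}.

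**The concern.** A Poisson model has no upper limit and sets the variance equal to the mean. Days abstinent cannot exceed 13 or 14, and their variance depends on two things: how close people are to the ceiling, and how strongly days within a person go together. There is no reason for it to equal the mean. A percent is not a count at all. If it is used as a Poisson response, the standard error depends on the unit chosen.

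The p-value enters the Benjamini-Hochberg set. If it is too small, the trial may claim an effect on drinking that is not there; if too large, it may miss one. The other four tests feel it too, but only slightly: the cut-offs are fixed by rank (0.01, 0.02, 0.03, 0.04, 0.05), so one bad p-value moves another by at most one rank. The same standard errors also set the confidence intervals, which matter even if the result is read only as an effect size.

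**Working it through.** **Inputs from the protocol.** Maximum count m = 13 ({20a}) or 14 ({12}). The sample size is stated "with a total of 76 participants", randomised 1:1, so 38 per arm. The protocol gives no figure for days abstinent to reproduce. Its 76 reproduces for the stated effect size of 0.66: a noncentral-t calculation needs 37.02 per arm, so 38.

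**Assumptions.** The protocol gives neither the mean proportion of abstinent days p nor the within-person correlation ρ (ICC). Both are varied. Days are taken as beta-binomial.

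**Step 1, standard error on the count.** The true variance is Var(Y) = m·p(1−p)·[1+(m−1)ρ]; Poisson assumes m·p. Hence

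model SE / true SE = √{ 1 / ((1−p)[1+(m−1)ρ]) }.

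Example, m = 13, p = 0.7, ρ = 0.3: (1−p)[1+12×0.3] = 0.3×4.6 = 1.38, and √(1/1.38) = 0.85. The ratio does not depend on the number of participants.

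| m = 13 | p = 0.5 | p = 0.7 | p = 0.9 |
|---|---|---|---|
| ρ = 0 | 1.41 | 1.83 | 3.16 |
| ρ = 0.3 | 0.66 | 0.85 | 1.47 |
| ρ = 0.5 | 0.53 | 0.69 | 1.20 |

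The ratio is 1 only at ρ = p/((1−p)(m−1)): 0.08, 0.19 and 0.75 for the three columns. The trial cannot know in advance on which side it will fall.

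**Step 2, the percent as response.** Rescaling days to 0–100 multiplies the mean by 100/m. The Poisson SE of the log ratio shrinks by √(m/100) = √0.13 = 0.36, while the true SE is unchanged. At ρ = 0 the ratios become 0.51 (p = 0.5), 0.66 (p = 0.7) and 1.14 (p = 0.9); at ρ = 0.3 they are 0.24, 0.31 and 0.53.

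**Step 3, false-positive rate.** Simulated with no treatment effect, 38 per arm, m = 14, unadjusted two-group test, nominal 5%, 10,000 trials per setting:

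| Mean, ICC | Poisson, count | Poisson, 0–100 percent | Quasi-binomial |
|---|---|---|---|
| 75%, 0 | 0.000 | 0.14 | 0.047–0.049 |
| 75%, 0.2 | 0.038 | 0.44 | 0.047–0.049 |
| 75%, 0.4 | 0.115 | 0.56 | 0.047–0.049 |
| 75%, 0.6 | 0.194 | 0.62 | 0.047–0.049 |
| 50%, 0.6 | 0.34 | 0.72 | 0.042 |

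For the 75% rows the quasi-binomial column shows the range over the four settings. At mean 90% the count analysis rejects in 0–3.8% for ICC up to 0.6. The 0–100 percent analysis rejects in about 2% at mean 90%, ICC 0.

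With the four covariates in the model (1,000 trials per setting, m = 13 and 14, p = 0.5–0.9, ρ = 0–0.5) the pattern is the same: count 0.000–0.31, percent 0.02–0.69, quasi-binomial 0.03–0.07, Poisson with robust variance 0.05–0.08.

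**Step 4, power for 75% versus 87% abstinent (m = 14).**

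| ICC | Poisson, default variance | Quasi-Poisson | Poisson, robust | Quasi-binomial |
|---|---|---|---|---|
| 0.1 | 63% | 91% | 92% | 90% |
| 0.2 | 61% | 75% | 76% | 74% |

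**The case against.** The strongest reply is that the fault lies in the variance, not in the Poisson family, and that the protocol states no variance option. Dispersion, offset and robust variance are commonly left to the analysis plan. This largely stands. A reader might infer that Poisson regression is unusable here and that only a logistic model will do; Step 4 and the robust-variance results show otherwise. What remains is that the protocol names this model and nothing that would correct its default.

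A reader might also infer that the percent analysis will always have standard errors far too small. The text does not support that. It holds only if 0–100 is the response. If percent means a rate with a log(days) offset, the results equal those of the count; if a 0–1 fraction is entered, the standard errors are far too large. Even on the 0–100 reading it fails near the ceiling with independent days. Moreover, {20a} lists the count, not the percent, as the tested measure, so the largest error rates do not clearly enter the Benjamini-Hochberg set.

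Third, the largest count-scale errors arise at 50% abstinence with strong clustering. Entry requires verified 48-hour abstinence, so high abstinence is plausible, and there the default Poisson is conservative. That is fair, but the cost is then lost power.

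Finally, the verb in {20a} is tentative, and the Discussion treats non-primary outcomes as providing effect sizes, not confirmation. Both points lower the weight. Yet the outcome is formally tested, and the Discussion also says that significant primary or secondary results would help justify a larger trial.

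**Conclusion.** The point holds at moderate severity. With its default variance, the only model named for days abstinent misstates the standard error of a count capped at 13 or 14, in a direction that cannot be known beforehand. Over assumed means of 50–90% and ICC of 0–0.6, the false-positive rate on the count runs from about 0% to 35%, against 4–5% with an estimated dispersion. At ICC 0.1, power for 75% versus 87% is about 63%, not 91%. These sizes rest on the assumed mean, ICC and beta-binomial form; that the default variance does not suit a bounded count does not depend on the particular values. The percent-scale range of about 2% to 72% is conditional on entering 0–100 as a count, which the text permits but does not state. The unseen analysis plan may already deal with the variance. The primary ISI analysis is not affected.

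**What to change.** Replace the model sentence in {20a} with wording such as:

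> Days abstinent out of days observed will be analysed by logistic regression with an estimated dispersion (quasi-binomial or beta-binomial), with treatment, site, sex and baseline ISI. The adjusted difference in percent days abstinent and its 95% confidence interval will be reported.

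Choose one of the two dispersion forms before unblinding. A Poisson model with a log(days observed) offset and robust or quasi variance is equally valid if the team prefers to keep the family. Do not use the 0–100 percent as a Poisson response. Replace the tentative verb by a fixed choice, name the same measure in {12} and {20a}, and reconcile "number and percent of days abstinent during the 13-day quit attempt period" with the 14 days in {12}.

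The cost is wording in the protocol and analysis plan, with no new data or participants. The one technical burden is that a logistic model works on the odds scale, so the difference in percent has to be derived from the fitted model.

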## Assignment of interventions: allocation

### Sequence generation {16a}

Participants will be randomized in a 1:1 ratio to suvorexant or matched placebo using a covariate adjusted randomization algorithm, stratifying allocation by site, sex, and level of sleep disturbance via the ISI score. This algorithm is implemented within REDCap and is run once study coordinators ensure participant signs the informed consent, is eligible for the study, and enters all stratification variables.

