
#### Clinician-administered assessments

Clinician-Administered PTSD Scale for DSM-5 (CAPS-5): Gold-standard in PTSD assessment. The CAPS-5 is a 30-item structured interview that can be used to make current (past month) diagnosis of PTSD, make lifetime diagnosis of PTSD, and assess PTSD symptoms over the past week [26–28].Clinical Institute Withdrawal Assessment Alcohol Scale Revised (CIWA-AR): This is a common instrument to assess and diagnose the severity of alcohol withdrawal, measuring 10 symptoms via a scale. This instrument takes about 2 min to complete and then scored by a medical professional. Cumulative scores of less than 8–10 indicate mild withdrawal. Next, scores of 8–15 indicate moderate withdrawal, and scores of 15 or more than 15 indicate severe withdrawal with impending possible delirium tremens.Mini-International Neuropsychiatric Interview for DSM-5: Assessment used to determine psychiatric diagnoses. This brief interview is structured and assesses DSM-5 current and lifetime psychiatric diagnoses. Note: Sections B, L, M, and MB will be omitted as these do not impact study inclusion/exclusion [29].Time-Line Follow-Back Assessment Method (TLFB): Interview technique that will be used to obtain quantity/frequency of alcohol consumption data for each day during the 30-day period prior to the study, throughout the period of study participation (measuring drinking on days outside of test session days) and the follow-up. Participants are given a blank calendar covering the time interval to be reconstructed and are asked to reconstruct retrospectively their drinking behavior over that interval. The process is facilitated by establishing anchor points (e.g., holidays, anniversaries, major national events). It can be scored to provide the number of days on which various levels of consumption occurred. The time-line method has good test-retest reliability and good validity for verifiable events. It has been used in numerous studies to compare pre- to post-treatment drinking [30].

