A mixed linear model for repeated measures will be used to estimate treatment differences for the change AUQ, PCL-5, and CAPS-5 scores from baseline to days 7 and 14. The model(s) will have fixed effects for treatment, time interval (as a categorical variable), treatment-by-time interaction, and the stratification effects of site, sex, and baseline ISI score. The baseline score for each outcome measure will also be included as a term in the model, as appropriate.

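### The two drinking outcomes are adjusted for baseline insomnia but not for pre-study drinking, although that is collected, which costs precision

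*Protocol article*

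**What the plan says.** Section {20a} of the protocol article sets out the primary model with terms for treatment, site, sex and baseline ISI. It then turns to drinking: "A similar model will also be run for the secondary outcome of mean number of drinks per drinking day". Days abstinent are given a Poisson fit on an exploratory footing, and the covariate list there reads "accounting for treatment, site, sex, and baseline ISI score". No drinking covariate is named for either outcome. Neither outcome is defined as a change from baseline, here or in Outcomes {12}; both are levels during the quit attempt.

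The repeated-measures models in the same section are used to "estimate treatment differences for the change AUQ, PCL-5, and CAPS-5 scores from baseline to days 7 and 14". For these, the article adds: "The baseline score for each outcome measure will also be included as a term in the model, as appropriate".

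Under Clinician-administered assessments, the Timeline Follow Back (TLFB) is used to "obtain quantity/frequency of alcohol consumption data for each day during the 30-day period prior to the study", as well as during participation. Randomisation works by "stratifying allocation by site, sex, and level of sleep disturbance via the ISI score" (Sequence generation {16a}); drinking is not a factor.

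**The concern.** The primary outcome and three of the five secondary outcomes are adjusted for their own baseline. Only the two drinking outcomes are not. Because they are levels, are not stratified on, and have no drinking covariate, the 30 days of pre-study drinking enter their stated analysis nowhere. Eligibility {10} requires moderate or severe AUD but sets no minimum or maximum amount of drinking, so participants may start from very different levels.

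How much someone drank before the study is the obvious candidate predictor of how much they drink in a two-week quit attempt. Leaving it out puts explainable variation into the error term. Both outcomes are formally tested under the false discovery rate procedure. The Discussion presents the alcohol outcomes as a source of effect sizes and says significant secondary results could help justify a larger trial. Wide intervals weaken both uses.

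**Working it through.** **The plan's own figure.** Sample size {14} gives 76 participants for a standardised difference of about 0.66, 80% power and two-sided alpha 0.05. An exact two-sample t-test needs 37.02 per arm, so 38 per arm and 76 in total: the figure reproduces, before attrition. It concerns ISI; no power is stated for drinking. (The worked example of 5.5 with SD 7 is a standardised difference of 0.79, not 0.66. That is a separate matter.)

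**Inputs.**
- Analysed sample: 76 × 0.93 = 70.7, taken as 70, or 35 per arm (attrition of up to 7%, {14}).
- Partial correlation r between the TLFB baseline and the outcome, given site, sex and ISI: not in the documents. Assumed range 0.2 to 0.7. The low end is plausible, because everyone must show 48 hours of abstinence before randomisation and then try to stop drinking.

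**Formula (linear model only).** Adding the baseline multiplies residual variance by 1 − r². The standard error and the detectable difference are multiplied by √(1 − r²), and the effective sample size by 1/(1 − r²). At r = 0.5, for example: 1 − 0.25 = 0.75; √0.75 = 0.866; 70/0.75 = 93.

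| r | Residual variance factor | Cut in SE | 70 analysed are worth | Detectable d, 80% power, 35 per arm | Power at an assumed d of 0.5 |
|---|---|---|---|---|---|
| 0 (as planned) | 1.00 | 0% | 70 | 0.68 | 54% |
| 0.2 | 0.96 | 2% | 73 | 0.67 | 56% |
| 0.3 | 0.91 | 5% | 77 | 0.65 | 58% |
| 0.5 | 0.75 | 13% | 93 | 0.59 | 66% |
| 0.7 | 0.51 | 29% | 137 | 0.49 | 82% |

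**Chance imbalance.** With 38 per arm, the between-arm difference in mean baseline drinking has SE √(2/38) = 0.23 SD. A difference of at least 0.3 SD corresponds to |z| ≥ 0.3/0.229 = 1.31, about 19% of the time. At least 0.4 SD corresponds to |z| ≥ 1.74, about 8%. Given a 0.3 SD imbalance, the unadjusted estimate moves by r × 0.3 SD: 0.06 SD at r = 0.2, 0.15 SD at r = 0.5 and 0.21 SD at r = 0.7. This is the same loss as in the table, seen in a single realised trial; it is not an additional harm.

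**Limits.** The formula does not carry over to the Poisson model for days abstinent, where the gain has the same direction but an unknown size. Drinks per drinking day has no value for a participant who never drinks in the quit attempt, so fewer than 35 per arm may contribute to that outcome.

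**The case against.** The wording is less settled than a closed covariate list. In the primary model, baseline ISI is both a stratification factor and the outcome's own baseline, so a similar model for drinks per drinking day could be meant to swap in baseline drinking. The Poisson model is only to be explored. Section {20c} says secondary outcomes are analysed by MMRM, and the MMRM paragraph in {20a} carries own-baseline terms. The full methods are deferred to an SAP that is not shown and may add the covariate. These points lower the confidence that baseline drinking is deliberately left out. They do not supply the term: the only list given names ISI, and the MMRM paragraph covers AUQ, PCL-5 and CAPS-5 only.

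Adjusting for the stratification factors is also a standard, valid analysis. That stands. The primary test is untouched, and the Discussion itself calls the alcohol outcomes provisional.

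A reader might infer that chance imbalance biases the treatment estimate. The documents do not support that. Allocation is randomised, so any imbalance is random error, already reflected in the standard error of the linear model. A reader might also take the upper rows of the table as the expected gain. Nothing in the documents supports a correlation that high, and at r = 0.2 the gain is slight.

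**Conclusion.** The point holds as one of efficiency. As written, the two drinking models omit the outcome's own baseline although it is collected before randomisation and the plan adjusts its other tested outcomes that way. Under an assumed partial correlation of 0.2 to 0.7, the linear model forgoes a cut of about 4% to 51% in residual variance, or about 2% to 29% in the standard error. The size within that range cannot be settled from the documents, and no figure is offered for the Poisson model. Imbalances of 0.3 SD in baseline drinking are fairly common at this sample size; those of 0.4 SD are not. Neither systematic bias nor an invalid test follows. Severity is minor to moderate, since the outcomes are secondary and not presented as confirmatory.

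**What to change.** Before unblinding, name the matching 30-day TLFB baseline in each model: baseline drinks per drinking day for mean drinks per drinking day, and baseline percent days abstinent for days abstinent. Keep treatment, site, sex and baseline ISI. If the SAP already does this, align the protocol wording with it. The cost is one degree of freedom per model and no new data collection. Because eligibility sets no drinking minimum, the wording should also say what value is used if someone reports no drinking day in the 30-day window.

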### Interim analyses {21b}

No formal interim analysis is planned; however, the study will be monitored by a Data Safety Monitoring Board (DSMB) committee. If the DSMB requests any sample size re-calculations or formal futility analyses, an addendum to the SAP will be made prior to implementation.

### Methods for additional analyses (e.g., subgroup analyses) {20b}

All primary and secondary outcomes will be explored for a sex by treatment interaction to determine if there is any signal of a differential treatment effect by sex. This interaction term will be included in models as a separate exploratory analysis goal. Since these analyses are exploratory in nature, no adjustment for multiple hypothesis testing will occur, and results will focus descriptively on point estimates and 95% confidence intervals (and opposed to *p* values to identify statistically significant differences).

### Methods in analysis to handle protocol non-adherence and any statistical methods to handle missing data {20c}

The intention-to-treat (ITT) population will be used for all planned analysis, with data from all participants analyzed according to the arm to which they were randomized irrespective of the amount of intervention received. This approach ignores noncompliance, protocol deviations, withdrawal, and lost-to-follow-ups. Analysis of the ITT population avoids overoptimistic estimates of the efficacy of an intervention resulting from the removal of non-compliers, accepting that protocol deviations occur in actual clinical practice.

Analysis of the secondary outcomes will be based on a mixed-effect model of repeated measures (MMRM) using data from all time points to account for missing data and thereby maximize information used for the analyses. These models treat missing data as ignorable missing, assuming any missing data are missing at random. No imputation processes will be used to replace missing data. However, every effort will be made to minimize missing data. Additionally, because missing observations have the potential to alter the results of analyses, we will examine whether the pattern of missing data is different among the groups.

